## Abstract

**Background:**

Depression is a high prevalence disorder, displaying high rates of lifetime incidence, early age onset, high chronicity, and role impairment. In Ireland 12-month prevalence of depression has been reported to be 10.3%. A large percentage of affected individuals have no medical diagnosis nor seek treatment. Cognitive Behavior Therapy (CBT) has established itself as an option for the treatment of depression. Many Irish adults with depression find it difficult to access evidence-based CBT, this is due to several factors, like stigma and costs. However, systematic factors including the shortage of trained professionals and the relative underdevelopment of services also make access difficult.

Stepped-care can increase access to evidence-based CBT. One option is tailored internet-delivered treatment programs. Preliminary research from Ireland needs now to include large-scale studies on effectiveness. Thus the current study seeks to examine the potential of an internet-delivered low-intensity treatment for symptoms of depression in an Irish adult community sample.

**Method/Design:**

The study is a randomized controlled trial of an online CBT (iCBT) program for the treatment of adults with depressive symptoms. The trial will include an active treatment group and a waiting-list control group. The active condition will consist of 8 weekly modules of iCBT, with post-session feedback support. Participants in the waiting list will receive access to the treatment at week 8. Participants will complete the Beck Depression Inventory (BDI-II) and eligibility criteria will also apply. Primary outcomes are depressive symptoms. Secondary outcomes include quality of life indicators, significant events and satisfaction with online treatment. Data will be collected at baseline and at post-treatment, week 8, and at follow-up week 20 (3-months) and week 32 (6-months). Analysis will be conducted on the intention-to-treat basis.

**Discussion:**

The study seeks to evaluate the effectiveness of an online delivered treatment for depression in a community sample of Irish adults with symptoms of depression. The study will be a first contribution and depending on the sample recruited the results may be generalizable to people with similar difficulties in Ireland and may therefore give insight into the potential of low-intensity interventions for Irish people with depressive symptoms.

**Trial registration number:**

Current Controlled Trials
ISRCTN03704676. DOI: 10.1186/ISRCTN03704676

## Background

Depression has been ranked high among the leading causes of disease burden throughout the world
[1], displaying high rates of lifetime incidence, early age onset, high chronicity, and role impairment
[2]. Twelve-month prevalence rates for depression in the U.S. have been estimated at 6.6%
[3], and in Europe 8.5%
[4]. In Ireland 12-month prevalence of depression as measured against DSM-IV criteria has been reported to be 10.3%
[4].

Studies have reported higher rates for women than for men, in Europe 12-month prevalence has been reported at 10.5% for women and 6.61% for men
[4]. Another European study that examined prevalence for older adults (65+) reported an overall 12-month prevalence rate of 12.3%
[5]. The study highlighted the traditional gender divide with women (14.1%) reporting a higher prevalence of depression than men (8.6%)
[5].

Epidemological studies have highlighted the occurrence of depression in younger age groups. A review of the literature posits the peak years for onset to be between 15–29 years
[6]. Prevalence rates and gender differences are relatively constant across the adult lifespan and given the earlier age onset would suggest that lifetime prevalence will be higher in the future for younger cohorts
[6].

Depression exacts significant economic, personal, intra-personal and societal costs. The economic costs alone are justification for accurately understanding and treating depression in individuals
[2,7,8]. Depressive disorders are associated with losses in quality of life and increased mortality rates
[9,10].

### Treating depression

The aetiology of depression is dependent on the individual and their biological and psychosocial predisposition. The relative importance of these factors vary across individuals. The current biologic understanding of depression posits that many aspects of depression can be understood in terms of dysregulation of the Central Nervous System (CNS) responses to stress and naturally dysregulation is influenced by a wide range of moderating variables such as genetics, age, sex, and developmental history. Science has been successful in identifying key neurobiological processes and developing medications to compensate for dysregulation in the CNS.

Depression can be treated successfully using antidepressants, but relapse is high following cessation, and many patients prefer psychological therapies
[11], which have proved equally as effective as antidepressants
[12]. By far the most extensively researched is cognitive-behavior therapy (CBT)
[13]. CBT has established itself as an option for the treatment of depression, for post-treatment gains and also for maintaining gains and preventing future relapses and recurrences
[14].

CBT is an amalgmation of cognitive science and behavioral science. A central construct is that of cognitive vulnerability, where certain beliefs constitute a vulnerability to depression
[15]. Such vulnerability has evolved out of peoples historical experience, the consequent core beliefs they hold about themselves, others and the world, and their information processing capabilities that are generally negatively attuned; each of which interact with the other to produce a cognitive vulnerabiltiy in the person
[16]. Research has provided compelling support for cognitive-vulnerability as theorized by Beck
[17] and demonstrates that cognitive-vulnerability increases the risk for first episode and recurrences of depression
[18].

Vulnerability is viewed as dormant until activated by some experience that has the effect of disrupting a person’s stability or physiological and psychological homeostasis. The cause can be either one major event or experience, or an accumulation of smaller experiences
[19]. Collectively they are grouped under the rubric of stress. The majority of research investigating possible links in depression consistently find a link between the experience of a stressful life event and the onset of depression
[20].

Cognitive-behavioral treatment consists of a range of cognitive and behavioral strategies that aims to correct distressing beliefs and thinking that occurs in information processing with depression prone individuals, in doing so distress is alleviated and strategies and skills are taught to help the person cope more effectively with life’s challenges
[16]. Treatment therefore includes self-monitoring and thought recording, behavioural activation, cognitive restructuring, challenging core beliefs, among others.

### Access to treatment

Worldwide, a large percentage of affected individuals have no medical diagnosis nor seek treatment
[21]. One study estimated the worldwide treatment gap in depression at 56.3%
[22]. Several barriers to accessing treatment exist, such as waiting lists, lack of motivation for change, negative perception of psychological and/or drug treatments, costs, and personal difficulty such as stigma; each can play an important role in choosing to seek diagnosis and treatment
[22,23]. Of those that may seek the help they need they are often met with a shortage of trained professionals and consequent waiting lists, which contradicts the benefits of early intervention
[24].

Many in Ireland with depression find it difficult to access appropriate and evidence-based CBT, this is due to several factors, some of which were mentioned earlier as barriers, but particularly in Irelands case, the shortage of trained professionals alongside the relative underdevelopment of services makes it difficult to access treatments
[25]. Many Irish present their psychological difficulties, initially, to their primary care phsician however, one survey reported that less than one third of GPs have postgraduate training in psychological therapies and 85% referred less than 5% of their service users with mental health difficulties to specialists
[26]. More recent reports also corroborate the state of affairs where less than 20% of patients presenting with mental health difficulties at Irish general practitioners are in receipt of secondary specialist services
[27,28].

### Stepped care models of treatment

In recent years attempts to overcome barriers to access have been addressed through the evolution of a new understanding in mental health care that recognizes high-intensity (e.g. face-to-face therapy) and low-intensity (e.g. bibliotherapy) services. Low-intensity interventions signify treatments that limit specialist therapist time, or use this time in a cost effective manner, for example, group treatments
[29]. To increase access to evidence-based psychological therapies it will be necessary to develop and deploy a stepped-care model where low-intensity interventions are provided as a first option, before referral to high-intensity interventions. Such a program is recommended as best-practice by the National Institute for Health and Clinical Excellence
[13] and also advocated by the Irish health service
[30]. Yet, despite the barriers that exist for Irish people, both personal and systemic, what is considered best-practice has not evolved in Ireland. Given the continued growth in high prevalence disorders (depression and anxiety) there is a real need to increase access. The experience of our neighbours in the UK through the Improving Access to Psychological Therapies program that uses a stepped-care model, introducing both low- and high-intensity interventions, has proven successful
[31].

### Delivering low-intensity interventions for depression

One of a range of low-intensity interventions is the development and delivery of tailored treatment programs for specific disorders using the internet, as both clinican-guided and self-administered interventions
[32]. Indeed CBT has proved a suitable evidence-based option for integration as a low-intensity intervention within a stepped care model
[33]. More precisely, low-intensity internet-delivered treatments for depression have established a sound base supporting their effectiveness and efficacy
[34]. In addition, such studies for depression treatment that provide human support yield enhanced results compared to those with no support
[34,35].

The internet offers the possibility of delivering a treatment intervention at low cost and perhaps overcoming some of the barriers to access mentioned earlier. The internet can deliver treatment incrementally and in an engaging way. Furthermore, internet penetration in Ireland is at 76.8%
[36] and it is likely that it is an attractive medium as people are already high users of the internet and related tools.

A number of small scale studies of online delivered treatments have been experimented with in Ireland
[37,38]. There is now a need to develop larger community based projects like those that have occurred throughout Europe to assess the feasibility, efficacy effectiveness and scalability of such low-intensity interventions for Ireland. Because high-intensity interventions cannot be delivered en-mass, Ireland, like its European neighbours, will have to consider the implementation of stepped-care that will include a broad range of low-intensity interventions as first options in care.

Therefore using established CBT principles informing skills and strategies for the management of depression in an integrated disorder-specific treatment plan, the study aims to deploy these using a novel computer-delivered software platform (SilverCloud) to help demonstrate its feasibility, efficacy and effectiveness as a low-intensity intervention for depression treatment. The platform being used integrates a number of innovative engagement strategies for improving the user experience: personal, interactive, supportive and social
[38]. The details of the platform and the content of treatment are described in more detail below.

### Dropout from online treatments

Although several online studies have reported benefits for users who have not completed the entire course of treatment
[39] it is still the case that dropout is a continued cause of concern, especially for self-administered treatments that do not involve a therapist or other form of support to users
[40]. Information to date on reasons for dropout is limited. Some studies have report variables such as difficulties using the computer, negative features of the program, perceived as too demanding, poor clinical progress, receiving alternative treatment, feeling better, lack of time, and problems understanding the computer program
[34,41]. These are useful and more indept exploration of these and other potential reasons is needed so as to inform both the development and adequate implementation of online delivered treatments. The SilverCloud platform that is been used in the current study has been designed by a multi-disciplinary team of computer scientests, clinical personnel, and academics. It therefore includes a number of engagement strategies for improving the user experience (personal, interactive, supportive and social) and supporting retention.

### Aware

Aware is a charity that aims to create a society where those with depression or related mood disorders, and their families, are understood and supported, are free from stigma and have access to a broad range of support options. The charity has existed since 1985 and their objectives are, first, to provide information and educate people about depression and mood disorders, their causes and consequences. Second, to provide emotional and practical support to individuals and their families. Third, to support research into understanding and treating depression.

They achieve their objectives through the provision of over 2,000 face-to-face support groups nationwide that are facilitated by trained volunteers. They have recently started a online support group, beginning in 2011 with 5 users rising to 15 at the start of 2012. They have a low-cost telephone line that in 2011 took over 19,000 calls, again all manned by trained volunteers. Aware is a well recognized and respected brand name in Ireland and receive some government funding with 80% of their funding raised from public donations. Their user group is national and numbers of users high, therefore they are well placed to collaborate in providing a low-intensity depression treatment for the community that will include support for participants.

### Objectives of the trial

The study aims to implement and evaluate the efficacy of an online self-administered treatment for depression, with support, for users of the Aware Charity that have depressive symptoms. The research questions are:

▪ First, can an online treatment for symptoms of depression be effective as a low-intensity community-based intervention for adult users with depression?

▪ Second, what do participants find helpful and hindering in their online treatment for depression symptoms?

▪ Third, are participants satisfied with accessing and using an online treatment for depression symptoms?

▪ Fourth, what are the reasons for dropout from an online treatment?

Based on the success that has been achieved with supported online treatments for depression
[34] we hypothesize that participants in the trial will demonstrate significant decreases in depressive symptoms post-intervention and a corresponding increase in quality of life indicators.

## Methods

### Study design

The study is a randomized controlled trial of an internet intervention for the treatment of depression. Participants will be randomized into two groups: the internet-delivered intervention with support and a waiting-list control group. The study protocol, information on the study, informed consent and related materials have been submitted and approved by the ethics committee at the School of Psychology, Trinity College Dublin (22/11/2013).

### Sample size

An analysis of a number of previous studies of an online intervention for depression in the community and that have used a CBT protocol similar to the intervention in the current study have reported post-treatment effect sizes averaging 1.29, and follow-up effects averaging 1.42, based on samples ranging from 45 – 300
[39,42-48]. We calculated power using G-Power software
[49], using a power of 0.80 and an alpha of 0.05, we would need 60 subjects in each arm of the trial to observe a moderate (*d =* .50) post-treatment difference.

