### Planned statistical analysis

The analyses will be based on the intention-to-treat principle, including those who began treatment and provided follow-up data irrespective of treatment compliance. Effects will be tested at the 0.05 level. All analyses will be carried out using SPSS. Baseline differences in demographic and clinical characteristics will be investigated using ANOVA. To assess for significant changes over time, repeated measures ANOVAs will be performed for the primary outcome measure for depression (BDI-II). In case of significant time x group interactions, contrasts will be conducted comparing changes from baseline to post-treatment for each group separately. Further any relationships between baseline sociodemographic data and outcomes on the primary outcome measure will be assessed. Repeated measures ANOVAs will also be used to assess any changes over time for secondary outcomes (GAD-7, EQ-5D and WSAS).

The magnitude of the within-group effects of each of the interventions (Cohen’s *d*) will be calculated using the pooled standard deviation. The magnitude of between-group effects will be established by subtracting the Cohen’s *d* statistic for the two groups
[63]. For Cohen’s *d* an effect size of 0.2 to 0.3 can be considered a small effect, around 0.5 a medium effect and 0.8 upwards, a large effect
[64].

Analysis will be made to determine the proportion of participants who make clinically meaningful change at end of treatment and at follow-up. An assessment of *remission* will be made using pre-treatment compared to post-treatment and follow-up scores on the primary outcome measure (BDI-II) and also for the secondary outcomes (GAD-7). The assessment of *remission* will consider the following cut-off scores for the primary outcome measure BDI-II score of <14
[50], and GAD-7 total score ≤8
[57] and and WSAS <10
[59]. In addition, using the post-treatment scores for depression (BDI-II) and anxiety (GAD-7) and dividing these with their pre-treatment scores a calculation of relative risk of depression and anxiety can be made
[58].

An index of *recovery* will be established by identifying the percentage of participants whom achieved a 50% reduction in pre-treatment compared to post-treatment score on BDI-II and GAD-7
[58]. In addition we will also calculate the number of reliably changed and recovered participants using Jacobson and Truax’s
[65] criteria.

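### Sixty per arm does not follow from the stated inputs (64 two-sided, 51 one-sided), and the text does not say whether 60 is before or after loss of outcome data

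*Protocol article*

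**What the plan says.** The Sample size section names G-Power as the software and gives the inputs and result in one sentence: "using a power of 0.80 and an alpha of 0.05, we would need 60 subjects in each arm of the trial", in order "to observe a moderate (*d =* .50) post-treatment difference". It names no test, sidedness, correlation between baseline and week 8, or allowance for loss.

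The Planned statistical analysis section says "Effects will be tested at the 0.05 level" and that "repeated measures ANOVAs will be performed for the primary outcome measure for depression (BDI-II") with attention to the time-by-group interaction. It calls the analysis intention-to-treat but defines the set as "including those who began treatment and provided follow-up data", whatever the participant's compliance with treatment.

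The Background section on dropout from online treatments says that "dropout is a continued cause of concern".

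**The concern.** The sample size sentence reads like a standard two-group calculation on post-treatment scores, and it gives enough to be checked. The familiar answer for d = 0.50, 80% power and two-sided 5% is 64 per arm, so 60 looks like a slip or a calculation with an undisclosed input.

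The second issue is what 60 counts. The analysis set excludes people without follow-up data. If 60 is the number randomised, each missing outcome takes power below a figure that is already short. If the claim stands uncorrected, a null result could be read as 80%-power evidence against a moderate effect when the true figure may be lower.

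**Working it through.** **Inputs.** From Sample size: power 0.80, alpha 0.05, d = 0.50, 60 per arm, equal allocation. From Planned statistical analysis: 0.05 level and ANOVA F tests, which are non-directional. Two-sided is therefore the natural reading, but it is an assumption because sidedness is not stated.

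**1. Attempt to reproduce 60.** Normal approximation, n per arm = 2(z₁₋α + z₁₋β)²/d², using α/2 for a two-sided test:

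- Two-sided: 2(1.960 + 0.842)²/0.25 = 62.8, so 63.
- One-sided: 2(1.645 + 0.842)²/0.25 = 49.5, so 50.

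Exact noncentral t: two-sided 63.8, so 64; one-sided 50.2, so 51. Neither sidedness gives 60.

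**2. What 60 analysable per arm delivers.** The noncentrality is d√(n/2) = 0.50 × √30 = 2.739 on 118 degrees of freedom. Two-sided power is 77.5% (78.2% by normal approximation). The d detectable with 80% power is 0.516. One-sided power would be 86%.

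**3. Unstated inputs that do reach 60.**

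- Change score: effective d = d/√(2(1 − r)), assuming equal SDs at baseline and week 8. At r = 0.53 this is 0.50/√0.94 = 0.516, giving 60 per arm.
- ANCOVA on baseline: effective d = d/√(1 − r²). At r = 0.25 this is 0.50/√0.9375 = 0.516, giving 60 per arm.
- One-sided t-test with 15% loss: 51/0.85 = 60.
- A between-groups repeated-measures test with a correlation of about 0.9.

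The text states none of these correlations, the one-sided test or the loss rate.

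**4. If 60 means randomised.** The document gives no loss rate, so the rates below are assumptions. Analysable n = 60(1 − loss), two-sided t-test, d = 0.50:

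| Assumed loss | Analysable per arm | Power | d detectable at 80% |
|---|---|---|---|
| 0% | 60 | 77.5% | 0.516 |
| 10% | 54 | 73% | 0.54 |
| 20% | 48 | 68% | 0.58 |
| 30% | 42 | 62% | 0.62 |
| 40% | 36 | 55% | 0.67 |

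**5. Power under a baseline-using analysis.** With two time points, the time-by-group interaction is equivalent to comparing change scores. At 60 analysable per arm its power is 70% at r = 0.4, 77.5% at r = 0.5, 80% at r = 0.53, 86% at r = 0.6 and 94% at r = 0.7. ANCOVA at an assumed r = 0.5 has residual variance 1 − 0.25 = 0.75 and effective d = 0.50/√0.75 = 0.577. Power is 88% with 60 per arm and about 80% with 48 (20% loss).

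**The case against.** The strongest objection is that the calculation may be under-described, not wrong. Sixty can be reached with ordinary inputs, so a reader who infers that no reasonable setting gives 60 goes too far. The planned analysis is also not a post-only t-test. Its power depends on a correlation that is not given, so the documents do not show that the trial as analysed falls below 80%; it could be lower or higher. Both points stand. Against them, the section describes a post-treatment difference and states no correlation, so the published inputs still do not yield the published number.

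A reader might also infer that people who stop treatment are dropped from the analysis. The text does not support that. The dropout section concerns not completing the course of treatment, and the analysis section keeps non-compliers who give data. Only those who did not begin treatment or gave no follow-up data are left out, and the dropout section does not tell us how many that will be.

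Nor does the text say that 60 is an enrolment target. It could mean analysable participants, and a separate recruitment figure could sit in the full protocol, which is not shown. This stands, and it is why the attrition figures are conditional. Sixty analysable per arm would still give 77.5%, not 80%, by the t-test.

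Finally, the section cites earlier effects averaging 1.29, at which even 36 per arm gives over 99.9% power. Those may not be between-group effects, and the trial was sized on 0.50, so the power claim has to hold at 0.50.

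**Conclusion.** The stated 60 per arm does not follow from power 0.80, alpha 0.05 and a post-treatment d of 0.50. On a two-sided t-test the shortfall is 4 per arm, or about 2.5 power points (1.8 by normal approximation), and the detectable effect moves from 0.50 to 0.516. That is all the document itself establishes, and it rests on reading the test as two-sided. One-sided would need 51, which does not match either.

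The larger losses of power, down to 68% at 20% loss for example, require two assumptions: that 60 means randomised, and the loss rate itself. They show why the missing statement matters; they are not a finding about the actual power of this trial. This is a correction to a stated figure, not a defect that should hold up the trial or a case for raising enrolment to 64.

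**What to change.** Reword the Sample size paragraph:

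- State that 60 analysable per arm gives about 77.5% power for d = 0.50 with a two-sided t-test at 0.05. Alternatively, give the test, sidedness and correlation that produced 60.
- Say whether 60 is the number randomised or the number analysable at week 8.
- Give power at an assumed rate of missing outcomes, labelled as an assumption (for example 68% at 20% loss of 60 randomised per arm).
- If a baseline-adjusted ANCOVA is adopted as the primary analysis, report its power with the correlation stated as an assumption: at r = 0.5, 88% with 60 per arm and about 80% after 20% loss.

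The cost is one rewritten paragraph and a less favourable power figure for the simple comparison. No added participants are needed. The Trial status section places the launch still ahead, so the change can be made before recruitment.
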